## Abstract

**Background:**

In 2003, the World Health Organization recommended exclusive breastfeeding (EB) during the newborn’s first 6 months of life and, if possible, during the first 2 years. However, EB rates resist these recommendations. In developed countries, only 1 out of 3 babies is breastfed during its first 6 months of life, and great differences between areas and countries can be observed. Only 35% of the newborns receive breastfeeding at 3–4 months of age. There are diverse strategies described in the literature that have proven their efficiency in improving breastfeeding rates. It has also been proven that professional support is an effective tool to extend any kind of breastfeeding; besides, it has been observed that mother-to-mother support also increases breastfeeding initiation, sustainment, and exclusive duration. The overall aim of the study is to assess the impact of the support groups on the sustainment of exclusive breastfeeding until 6 months after birth.

**Methods/design:**

This study is a cluster-random multicentric clinical trial with a control group and an intervention group, without blinding because it is impossible to mask the intervention. A randomization by centres of primary health (clusters) will be carried out. The women allocated to the intervention or control group will be randomized with a simple randomization sampling. The participants’ breastfeeding rate will be followed up at the first 10 days, and at 2, 4, and 6 months of their newborn’s life.

**Discussion:**

There is a need to assess the impact of mother support groups on exclusive breastfeeding. This study aims to analyse the outcomes related to the support received and to identify what should the structure of these groups be; in other words, to describe factors related to a better breastfeeding experience in order to help women increase breastfeeding rates.

**Trial registration:**

The trial is prospectively recorded at the ISRCTN registry (Trial ID: ISRCTN17263529). Date recorded: 17/06/2020.

## Background

In 2003, the World Health Organization (WHO) recommended exclusive breastfeeding (EB) during the newborn’s first 6 months of life and, if possible, during the first 2 years [1]. Breastfeeding is considered the best option to feed newborns due to its multiple properties. However, EB rates resist these recommendations. In developed countries, only 1 out of 3 babies is breastfed during its first 6 months of life, and great differences between areas and countries can be observed [2]. Only 35% of the newborns receive breastfeeding at 3–4 months of age [3].

The percentage of newborns that initiate breastfeeding in their first hour of life has significant importance, since it has been proven that early initiation of breastfeeding after birth is associated with a longer duration of this practice [4]. Despite all the benefits that have been described in the previous literature, for the mother as well as for the newborn at a physical and psychosocial level [5–8], breastfeeding rates after hospital discharge are roughly 71% [9], with a considerable decrease in the first weeks of the newborn’s life, reaching 25% at 6 months postpartum [10]. However, some studies suggest that these women felt disappointed because they could not prolong breastfeeding any longer. Usually, women who ceased breastfeeding after the first 6 weeks postpartum would have wanted to continue for longer, as well as those who breastfed for at least 6 months [1]. The main reasons described were lack of knowledge and of milk production [2]. Thus, it is brought to light that women have a positive inclination to continue breastfeeding but, due to diverse reasons, they are forced to give it up.

A recently published systematic review (2015) identifies the barriers and facilitators related to breastfeeding sustainment; experiences with previous births, certain birth-related hospital practices, or the fact that the mother had been breastfed by her own mother are some of the factors that condition the current breastfeeding experience [11].

Furthermore, there are also factors such as maternal age, schooling level, family support, multiparity or antenatal lessons, that can condition prolongation [12]. On the other hand, it has been observed how other collectives are more vulnerable to breastfeeding sustainment, such as those who have a low socioeconomic status or immigrants, who require greater support from the health professionals [13].

Some studies have been carried out assessing the strategies that can increase mother adherence to breastfeeding, and a positive effect was observed. Professional support has been proven to be effective in order to extend any kind of breastfeeding, but the effects on EB are less clear [11, 14]. Besides, it has been observed that mother-to-mother support for breastfeeding also increases breastfeeding initiation, sustainment, and exclusive duration [15].

The types of support described in the studies are diverse: from educational interventions to advice during home visits, support among breastfeeding mothers, telephone support, and educational programs on the Internet, as well as breastfeeding advice during the mother’s stay at the hospital [2, 16]. All these studies have proven to be effective in some way, but it has also been concluded that we need more studies assessing the effectiveness of professional and non-professional support in different contexts, particularly in communities with low rates of initiation and sustainment of breastfeeding, and in women who desire to continue for more than 3 months [17].

For this reason, we outline this study, which aims to assess the impact that joining breastfeeding support groups has on breastfeeding sustainment and prolongation in primary health centres of the Spanish Autonomous Community of Andalusia.

## Methods/design

The overall aim of the study is to assess the impact of the support groups on the sustainment of exclusive breastfeeding until the first 6 months after birth. More specifically we will:
Determine factors related to breastfeeding sustainment.Identify the motivators of breastfeeding interruption in infants during the first 6 months of life.Describe the main problems consulted by women in the breastfeeding support groups.Compare the strategies of face-to-face and virtual ante/postnatal sessions with only postnatal sessions regarding breastfeeding sustainment.Know the influence of these support groups on the perceived self-efficiency of breastfeeding.

### Study design

This is a multicentric cluster randomized controlled trial with a control group and an intervention group, without blinding. This protocol has been written according to the recommendations of the SPIRIT 2013 statement [18, 19], a guideline that defines the standard elements of a protocol, including recommendations for intervention trials, which can be found in Additional file 1. Besides, the design of this clinical trial follows the requirements of the CONSORT statement.

#### Participants, recruitment, and study area

Eligible female participants will be recruited in randomized primary health centres (clusters) in Andalusia, Spain. Andalusia is an Autonomous Community divided into 8 provinces with a total of 8,414,240 inhabitants (available data in 2019) [20], with a birth rate of 8.48 for each 1000 inhabitants (2018) [21]. By July 1st, 2019, the number of females in a reproductive age in Andalusia was 1,924,680 [22]. This is a multicentric study based on the Andalusian provinces of Seville, Huelva, Cádiz, Granada, and Jaén. Participant recruitment will be conducted on the antenatal care clinic at the 35th–37th week of pregnancy. Midwives will explore the women’s intentions regarding breastfeeding and whether or not they meet the inclusion criteria described below; they will also explain to them the purpose of the study including its risks and benefits. The women will be invited to participate voluntarily.

The eligibility criteria will be revised in the first postpartum visit for the women who accept to participate in both the control and the experimental groups.

Midwives meeting the criteria described below will serve as trained recruiters:
At least 2 years of professional experience as a midwifeNot having the intention of abandoning the work centre during the project time periodAttendance to the project’s training meetingSignature of the research agreement

#### Inclusion criteria

Healthy women with exclusive or partial breastfeeding 10 days after birth, and who attended antenatal lessons in the Primary Health CentreWomen over 18 years of ageWomen who accepted and signed the informed consent

#### Exclusion criteria

HIV positiveCancerTuberculosis infectionNo intention to breastfeedImpossibility or contraindication to breastfeed due to medical conditionsCommunication difficulties due to language

#### Randomization and data management

Centres are randomized to either an intervention arm or normal care. After this randomization, women are allocated either to the intervention group or to the control group by simple random sampling at the 35th–37th week of pregnancy by the midwives at the primary health centres, who will confirm that these women have the intention to breastfeed and that they have indeed initiated it in the first 10 days postpartum. Once the centre randomization for the recruitment of women for the control and intervention groups is conducted, these will be once again randomized following a simple randomization strategy. The participants’ recruitment will begin in September 2020, and will end in March 2022. This will be carried out by those midwives responsible for each health centre, being advised by one of the project’s experts.

These experts will work independently of the accountable researchers for the recruitment of participants. They will allocate health centres using a random sequence made by the *Oxford Minimization and Randomization (OxMAR)* system [23]. The experts will randomly assign a non-transferrable identifier to the health centres, making a difference between the control group and the experimental group centres. Subsequently, each participant will have an identification code depending on their group. This way, we intend to avoid the bias between two women attending antenatal care at the same centre who may or may not join the breastfeeding support group linked thereto, depending on whether they are allocated to one group or the other.

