#### Data collection

Once the woman is randomized to the control or intervention group and has signed the written consent, having been previously informed of the study objectives, the midwife will let her know about the follow-up she will need to perform throughout the study. The woman will have to choose whether she prefers to be followed up via the GALMA Project application (App), or by filling in online questionnaires via WhatsApp®.

The previously mentioned basal follow-up will be conducted and the participants will have to facilitate the information using the study App, which will have previously sent a reminder message to them. Those women who opt to fill in online questionnaires will receive a phone call the previous day from a member of the research team, who will send to them the link to the questionnaires. Data related to the monitoring, both electronic and via the App, will be coded and saved by the research team. Those data related to obstetrical results and those derived from a hospital stay will be drawn from the patient’s medical record, after the patient’s consent.

Incorrect or missing data will be checked by the members of the research team and the participants will be asked for their fulfilment. All data will be recorded in an electronic database with access only by the team members. Hard copies of the participants’ questionnaires will be kept in a safe and secure file which can be accessed only with previous authorization.

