### Analysis

A complete statistical analysis plan will be previously performed, as well as a report thereof and of the results, according to the Consolidated Standards of Reporting Trials (CONSORT) [35, 36]. The analysis will be carried out on the basis of an intention-to-treat principle, without taking into account whether or not adherence to the breastfeeding support group was completed. Individual health centres are the randomization units and the mother-newborn dyad will be the analysis unit. All statistical trials and confidence intervals will be assumed with a type I error established in alpha = 0.05, using the IBM SPSS V22 statistics package [37].

An exploratory data analysis will be conducted in order to identify atypical values, for the total of our studied sample, as well as for the different sub-groups created. A graphic exploratory analysis of the different studied variables will also be conducted, according to their numerical or non-numerical character. Frequency and percentage distribution scales will be elaborated for the descriptive analysis of variables with a qualitative (non-numerical) character. For the quantitative (numerical) ones, centralization and dispersion measures will be calculated. In variables with a normal distribution, the mean and the standard deviation will be calculated and, in those with an asymmetric distribution, the mean and interquartile range (p25-p75) will be calculated. Furthermore, point estimators and confidence intervals will be calculated at 95% for averages and percentages. The relationship between two qualitative variables will be analysed with Pearson’s chi-square test, the correction for continuity of the chi-square test, a linear-by-linear association test, and Fisher’s exact probability test, based on the application criteria. The significant results of these tests will be complemented with a confidence interval set at 95% for percentage differences.

Regarding the numerical variables between two groups, the Student’s t-test of independent samples for mean comparisons will be carried out, once the requirements of randomness, normality (Kolmogorov-Smirnov’s test, or Shapiro-Wilks’ test, according to the sample size) and equality of variances (Levene’s test) are validated. In case this one is not achieved, the Student’s t-test for independent samples with Welch’s correction will be carried out. In case normality requirements are not accomplished, the Mann-Whitney’s U test will be applied.

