### Ethics and dissemination

This study has been elaborated in strict compliance with the ethical principles of the Declaration of Helsinki (1964), subsequently revised in Tokyo (1975), Venice (1983), Hong Kong (1989), Somerset West (1996), Edinburgh (2000), Washington (2002), Seoul (2008), and Fortaleza (2013), including the informed consent request for the women participating in it.

Participation in the project is voluntary, as well as the participation request. The study has been laid out according to Spanish regulation act No. 14/2007 of July 3rd, regarding biomedical research, complying with the protocol suitability requirements and with the procedure regarding the study objectives. In the same way, the study will be conducted according to the Declaration of Helsinki.

All patient-related data collected for this study will be treated according to the Spanish Organic Law on Protection of Personal Data (Spanish Organic Law 15/1999) of December 13th and to European Regulation (EU) 2016/679 of the European Parliament and Council of April 27th, 2016, as well as to the established confidentiality and anonymity rules.

A written informed consent was provided to every participant in the study. The women were informed of the study objectives before being allocated to an arm.

The study was approved by the Research Ethics Committees of the Virgen Macarena and Virgen del Rocío hospitals (Seville, Spain) on February 24th, 2020 (Code 1936-N^− 19^).

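### Centres are randomised to arms, yet women are also described as individually randomised to arms, and nothing says which step decides a woman's arm

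*Protocol article*

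**What the plan says.** **The centre is the unit.** Study design labels the trial cluster randomised. Randomization and data management opens with "Centres are randomized to either an intervention arm or normal care". Its second paragraph has independent experts allocate centres with the OxMAR system, label each centre as control or experimental, and give each participant a code that depends on her group. The stated purpose is that "we intend to avoid the bias between two women attending antenatal care at the same centre" who might or might not join that centre's support group. The Analysis section agrees: "Individual health centres are the randomization units and the mother-newborn dyad will be the analysis unit".

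**The woman is the unit.** The same Randomization section continues: "After this randomization, women are allocated either to the intervention group or to the control group by simple random sampling", at 35 to 37 weeks and by the centre midwives. It then adds that "these will be once again randomized following a simple randomization strategy". The Abstract (Methods/design) says "The women allocated to the intervention or control group will be randomized with a simple randomization sampling". Data collection begins "Once the woman is randomized to the control or intervention group and has signed the written consent".

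**Timing of information.** Ethics and dissemination says "The women were informed of the study objectives before being allocated to an arm", without saying whether this means the centre's allocation or a step at the woman's level.

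**The concern.** If the centre's arm settles a woman's arm, there is nothing left to randomise at her level. If she is drawn individually into intervention or control, the centre's arm settles nothing. The text prescribes both and gives no rule for a woman whose draw differs from her centre's label.

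Three things depend on the answer:

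- **Contamination.** Individual allocation places both arms in one centre. According to Description of the intervention, the midwife leads and moderates the support group, and control women may book on-demand appointments with the reference midwife of their own centre. The trial is unblinded. This is the situation that centre allocation was meant to prevent.
- **Concealment.** The centre step uses a sequence handled by experts who are independent of recruitment. The individual step is placed with the recruiting midwives, and no concealment is described for it.
- **Sample size and analysis.** Whole-centre allocation and individual allocation within centres call for different variance calculations, so whether 512 women is enough depends on which was meant.

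**Working it through.** **1. The texts side by side**

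| Place in the protocol article | Unit that receives an arm |
|---|---|
| Study design | Centre (cluster) |
| Randomization and data management, first sentence | Centre |
| Same section, next sentence and the once-again sentence | Woman, after the centre step, by midwives |
| Same section, second paragraph | Centre, with the same-centre safeguard |
| Analysis | Centre |
| Abstract, Methods/design | Woman |
| Data collection | Woman |

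The woman-level wording stands in three separate places, so it is not a single slip. The contradiction needs no arithmetic. The calculations below only show what is at stake.

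**2. The plan's own figure**

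Inputs from Study sample size: 25% in controls, an increase of 12 points (37%), two-sided 5%, power 80%, loss 10%.

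Unpooled formula: n = (1.960 + 0.842)² × (0.25×0.75 + 0.37×0.63) / 0.12² = 7.849 × 0.4206 / 0.0144 = 229.3, so 230 per arm. Then 230/0.9 = 255.6, so 256 per arm and 512 in total. This matches the stated figure. The pooled formula gives 232, and 232/0.9 gives 258. Both are formulas for individually randomised trials, with no design effect.

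**3. If women are individually allocated within centres**

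Assumption, not in the documents: a share c of controls is exposed to their centre's group and gains the full 12 points. The control rate becomes 0.25 + 0.12c. Power is that of the pooled z-test at 230 evaluable per arm:

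Φ{ [d√n − 1.960√(2p̄(1−p̄))] / √(p₁(1−p₁) + p₂(1−p₂)) }

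| c | Control rate | Difference | Power |
|---|---|---|---|
| 0 | 25.0% | 12.0 points | 80% |
| 10% | 26.2% | 10.8 points | 70% |
| 25% | 28.0% | 9.0 points | 54% |
| 30% | 28.6% | 8.4 points | 48% |
| 50% | 31.0% | 6.0 points | 27% |

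For c = 30%: d√n = 0.084 × √230 = 1.274; (1.274 − 1.960 × 0.664)/0.661 = −0.041; Φ(−0.041) = 0.48.

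**4. If the centre alone sets the arm**

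Assumptions, not in the documents: m = 10 to 30 women per centre and an intracluster correlation of 0.01 to 0.05. Design effect = 1 + (m − 1) × ICC.

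- m = 10, ICC 0.01: design effect 1.09; 232 × 1.09/0.9 gives 281 per arm; power with 230 evaluable per arm is about 76%.
- m = 30, ICC 0.05: design effect 2.45; 232 × 2.45/0.9 gives 632 per arm; power with 230 evaluable per arm is about 43%.

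Steps 3 and 4 belong to different readings. Their losses should not be combined: step 3 needs both arms in each centre, where the design effect for whole-centre allocation does not apply in the same way.

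**The case against.** The strongest reply is that this is loose language and not a second allocation. The design label, the Analysis section, the OxMAR step and the group-dependent codes all point to the centre. Random sampling is a term for selecting people, and the Abstract sentence can be read as selecting among women whose arm is already set. On that reading midwives only choose whom to recruit within a centre of known arm.

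Part of this stands. The document as a whole leans towards the centre, and recruitment sampling may well be what was intended. It does not remove the problem. Selecting women for recruitment does not allocate them to one group or the other, is not a repeat randomisation, and does not fit the opening of Data collection. A midwife who followed the words literally would run a different trial.

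Three stronger readings are tempting but not supported:

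- **That the Ethics statement on prior information is false.** It is ambiguous. A woman could be informed before she receives her group code even though her centre's arm was fixed earlier.
- **That the midwife-run draw is unconcealed.** The article says only that midwives carry it out, advised by a project expert. Concealment is not described, which does not show that it is absent.
- **That power will be 48%, or any other single value.** The exposure shares, and the full effect in exposed controls, are assumptions.

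It should also be said that only Randomization and data management gives the same-centre rationale. Study design and Analysis state the design or unit without a reason.

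**Conclusion.** The contradiction is real and lies in the current text. The article gives two incompatible allocation rules and no rule for choosing between them. Read literally, it defeats the safeguard it states. An analysis plan written later cannot settle this, because the unit of allocation has to be fixed before the first woman is recruited.

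The size cannot be derived from the documents. Under individual allocation with assumed control exposure of 10% to 50%, power falls from 80% to between about 70% and 27%. Under centre allocation with the assumed centre sizes and correlations, it lies between about 76% and 43%. These ranges show why the answer matters and are not forecasts. A reader might infer that the trial will actually run with both arms in each centre. The documents do not establish that, only that they instruct it in some places and rule it out in others. The correction must be made before recruitment.

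**What to change.** - In the Abstract (Methods/design), Randomization and data management, and Data collection, state that a woman's arm is the arm of her centre and that the OxMAR centre list is the only allocation step. This agrees with Study design and Analysis.
- Delete the repeat randomisation and the wording that allocates individual women. If women are only selected within centres, say sampled or invited.
- In Ethics and dissemination, state whether women are informed before or after their centre's arm is fixed.
- With the centre confirmed as the unit, check the 512 and the planned analysis for clustering, and restate the power if needed.

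The allocation correction costs wording only and removes a step. The follow-on check may cost more: 512 reproduces only without a design effect, so the result may be a larger sample or a lower stated power.
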